### Randomization

A computerized random number generator (sealed envelope™) was used by the study principal investigator (PI) and coordinator at Duke-NUS to create an assignment schedule to allocate eligible participants into one of the two study arms in ratio of 1:1. Randomization was stratified according to the number of glaucoma medications prescribed to patients (one versus multiple eye drops) given that medication adherence has been shown to be highly correlated with this factor [44]. For allocation concealment, the study PI and project coordinator enclosed the assignments in sequentially numbered, opaque, sealed randomization envelopes before handing them to the research optometrist on site. Blocking size will not be disclosed to the study site to protect concealment. Note that the behavioural nature of the intervention precludes masking the arm allocation to both the study team and patient. Arm allocation will be revealed at the end of the 1-month baseline measurement of medication adherence (see Fig. 2).

**Fig. 2 Fig2:**
[figure not shown]
SIGMA patient timeline

### Patient recruitment, retention, withdrawal, and discontinuation

During routine clinic visits at SNEC, ophthalmologists will identify patients with problems adhering to their glaucoma eye drops and check that their GSS score does not exceed 4. The ophthalmologists will then refer the patients to a trained research optometrist to verify eligibility, take informed consent, and proceed with enrolment. Trained site research coordinators will also assist with consent taking and administer study questionnaires when required. Referral can also occur through nurse counsellors at the SNEC Glaucoma Counselling Clinic (GCC) where some non-adherent patients are referred to by their ophthalmologists. Recruitment is planned to last a year. As an incentive to join the study, patients will receive a SGD10 voucher upon successful enrolment.

Patient retention in the trial will be promoted by financial incentives. Patients will receive SGD10 when they join the study, they will also receive SGD20 for returning their eCAP(s)™ at month 3, and SGD30 at the end of the study for completing the month 6 assessment and returning the eCAP(s)™. Patients will also be engaged by means of a short adherence report they will receive at month 3 and month 6. Patient burden will be minimized by the use of a courier service to collect and return the eCAP™ in lieu of a clinic visit for the month 3 medication adherence assessment. Lost devices or broken devices will be replaced free of charge to enable the patient to continue participating in the study.

Patients are free to withdraw from the study at any time. When possible, the research optometrist will administer a short exit questionnaire to inquire about the reasons of the withdrawal and collect the study devices from the patient. Patients who withdraw will receive SGD15 for returning their eCAP(s)™ and SGD15 if they agree to complete a short exit questionnaire. In addition, patients will be discontinued from the study when their glaucoma condition deteriorates to the point of requiring surgical intervention or when they develop significant comorbid conditions that lead their ophthalmologists to discontinue their topical medications or prevents application of medications without assistance.

### Data collection

In order to record medication adherence, each patient will be issued with up to three eCAPs™ depending on the number of glaucoma medications the patient is prescribed. Each device will be labelled with a number, based on when the study device is set up and will run in ascending numerical order (the number will not relate to the patient’s unique ID number). Each vial will be labelled with the name of the patient and the medication. For patients with multiple medications the research optometrist will explain to the patient which eCAP™ number corresponds to which medication. This will be written into the patient instruction booklet (see Additional file 1) for ease of reference for patients. The research optometrist will explain to the patient how to use the eCAP™ and test that the device is properly working before the patient leaves the clinic. The patient instruction booklet also provides information on eCAP™ use along with the contact information for the study team at SNEC and Duke-NUS in case patients have any questions about their device. Patients will also be reminded to report any loss or malfunction of their devices to minimize data loss. If the patients report any issue with their devices, a replacement will be immediately arranged by courier service. In addition to receiving calls to reveal randomization and arrange device collection and delivery, the patients will receive three follow-up calls (see patient timeline, Fig. 2). During all calls, proper use and working condition of the devices will be checked. For multiple medication users, it will also be verified that the correct medication is stored in the correct vial. For further quality assurance, a copy of the eye drop dosing schedule and instructions on eCAP™ use will be sent along with the eCAPs™ and brief medication adherence report after the month 3 assessment.

IOP will be measured using Goldmann Applanation Tonometry (GAT). At baseline, the ophthalmologist will take the IOP at the point of referral. The research optometrist will then record this measurement in the baseline checklist. The same workflow will be followed at month 6 unless it is not possible to make this assessment coincide with the patient’s clinic visit. In such event, the research optometrist will take down the IOP that was taken closest to the month 6 visit from the patient’s medical record.

Paper-based questionnaires will be used at baseline and month 6. Both questionnaires include the GQL-15 and EQ-5D-5 L instruments. The baseline questionnaire also records the BIPQ and BMQ instruments along with patient socioeconomic characteristics. The month 6 questionnaire also includes the patient’s MMAS responses and score. These questionnaires will be self-administered unless the patient has difficulties in which case it will be administered by the research optometrist.

In addition, the research optometrist will fill out paper-based checklists at baseline and month 6. In addition to the patient’s IOP, the baseline checklist will record the patient’s medication regime extracted from medical records. The month 6 checklist will record the patient’s understanding and self-reported compliance to the study. The paper-based screener will also contain the self-reported MMAS responses and score.

All study documents are available in English and Mandarin to ensure the study is open to a wide range of the patient population. The research optometrist will check for completeness of all study documents and questionnaires on site and the Duke-NUS study team will double-check this at the data entry point and follow up in the event of any missing data. In efforts to promote compliance to the study requirements, all patients will receive a small monetary reward for providing key study data, as previously described - SGD10 upon successful enrollment, SGD20 for returning the eCAP™ at month 3 and SGD30 for completing the month 6 assessment and returning the eCAP™.

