#### Arm 1: usual care (UC)

Patients attend routine check-ups with an ophthalmologist where they have glaucoma eye drops prescribed for them, which they then purchase at the SNEC pharmacy. The frequency of check-ups varies between patients depending on the severity of their condition. The decision is made by the ophthalmologist on how regularly patients should return for check-ups, ranging from 3 months to once a year. IOP and visual acuity are measured at every visit while visual field readings are taken annually. Non-adherent patients may also be offered glaucoma counselling if necessary. During a counselling session, a nurse delivers an educational component on effective glaucoma treatment. Counselling includes the following components: (i) understanding of glaucoma and visual field process with a focus on risk factors and symptoms, (ii) management and treatment of glaucoma, (iii) medications usage with practical advice on self-application of eye drops. In addition, the nurse counsellor determines a dosing schedule for each medication that accommodates the patient’s lifestyle and takes into account working hours. During this discussion, the nurse counsellor underlines the health risks raised by non-adherence to the medication regimen.

In order to properly identify the effect of value pricing, we brought the following deviations to usual care. First, a short adherence report will be sent to the participants as described above. Second, a non-contingent payment of SGD30 will be made to them at months 3 and 6. However, unlike VP patients, no financial incentive will be given when they are adherent to their medications.

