#### Secondary outcomes

*Monthly mean change from baseline in percentage of adherent days at months 2 to 5* in order to monitor adherence trajectories before the study end point (month 6).*Monthly change from baseline in the proportion of patients with percentage of adherent days greater or equal to respectively 75 % and 90 % over the study period (i.e. from month 2 to 6)*. These outcomes are of interest as they are defined according to the adherence thresholds that VP patients need to meet in order to receive their financial incentives.*Mean change from baseline in IOP at month 6*.*Mean change from baseline in GQL-15* [38] *score at month 6* as a glaucoma-specific measure of quality of life.*Mean change from baseline in EQ-5D-5L* [39] *score at month 6* as a generic measure of quality of life.*Mean cost of financial incentives at month 6 in the VP arm. Individual cost of financial incentives will be calculated using the participants’ monthly glaucoma-related healthcare costs recorded at baseline and percentage of adherent days at month 6 (i.e. primary outcome).*

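### The fallback for month-6 IOP has no time limits and does not exclude the baseline reading, so some patients can be given a change of exactly zero

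*Protocol article*

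**What the plan says.** IOP is the outcome for secondary objective 1, listed under Secondary outcomes as "Mean change from baseline in IOP at month 6". Under Secondary analyses, the change is regressed on study arm, baseline IOP and the other baseline characteristics.

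The Data collection section fixes where the two readings come from. For the first, "At baseline, the ophthalmologist will take the IOP at the point of referral". The same workflow applies at month 6 "unless it is not possible to make this assessment coincide with the patient’s clinic visit". In that case "the research optometrist will take down the IOP that was taken closest to the month 6 visit", taken from the medical record.

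Three other statements bear on what that record will hold:

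- Recruitment takes place at clinic attendances: "During routine clinic visits at SNEC, ophthalmologists will identify patients" (Patient recruitment, retention, withdrawal, and discontinuation).
- Check-up intervals are set by the ophthalmologist, "ranging from 3 months to once a year" (Arm 1: usual care).
- The record gains IOP values at those check-ups: "IOP and visual acuity are measured at every visit" (same section).

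Allocation is revealed one month after enrolment, and the intervention then runs for five months (Study arms).

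**The concern.** The baseline IOP is itself a clinic reading and sits in the same record that the fallback searches. The rule asks only for the reading nearest to month 6. It has no earliest date, no latest date and no exclusion of the baseline value. A patient whose next check-up falls after month 6 has no newer reading on file when the month-6 checklist is completed. Followed literally at that moment, the rule returns the baseline value, and the change is 0 whatever the arm and whatever happened to the eye.

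Such zeros carry no information about the intervention and pull the arm comparison towards no difference. If the optometrist waits for the next visit instead, the reading reflects a period without incentives. The protocol's Discussion itself says that adherence gains tend to fade once incentives stop. Because the rule does not choose between these options, the choice falls to staff who know the allocation.

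**Working it through.** **Inputs.** Check-up interval of 3 to 12 months, IOP recorded at check-ups, and baseline reading at month 0 (Arm 1: usual care; Data collection). Allocation revealed at month 1 and incentives ending at month 6 (Study arms). The article gives no IOP effect, standard deviation, power or fallback share, so there is no IOP figure to reproduce. The sample size of 100 is for adherence. It is used here only to set 100 × (1 − 0.20) / 2 = 40 analysed patients per arm.

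**Step 1: which reading the rule returns.** Visits are counted from the baseline clinic visit at a constant interval.

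| Interval (months) | Closest reading on record by month 6 | Closest reading if later ones count |
|---|---|---|
| 3 | month 6 | month 6 |
| 4 | month 4 | tie, months 4 and 8 |
| 5 | month 5 | month 5 |
| 6 | month 6 | month 6 |
| 7 | **month 0** | month 7 |
| 8 | **month 0** | month 8 |
| 9 | **month 0** | month 9 |
| 12 | **month 0** | **tie, months 0 and 12** |

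Intervals of 10 and 11 months behave like 7 to 9. The later visit is 4 or 5 months from month 6, against 6 months for baseline. So under the first reading of the rule, every interval longer than 6 months returns baseline. Under the second, only 12 months can do so, through a tie with no tie-break. Intervals of 7 to 11 months then give a value taken 1 to 5 months after incentives end.

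**Step 2: effect on the comparison.** Let the true mean changes be μ(VP) and μ(UC), with a share f in each arm given a change of 0. The expected difference is

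(1 − f) μ(VP) − (1 − f) μ(UC) = (1 − f) [μ(VP) − μ(UC)].

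This assumes the same f in both arms and that affected patients would otherwise have had the average effect.

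**Step 3: simulation of the planned regression.** Change was regressed on arm and baseline, with 40 per arm and 6,000 trials per setting. The baseline/month-6 correlation was assumed to be 0.6, and the effect was set to give about 78% power at f = 0. The values of f are assumed.

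| f (assumed) | Estimate ÷ true effect, baseline reused | Power, baseline reused | Power, treated as missing |
|---|---|---|---|
| 0% | 1.00 | 78% | 78% |
| 10% | 0.90 | 73% | 73% |
| 20% | 0.80 | 65% | 68% |
| 30% | 0.69 | 57% | 61% |
| 50% | 0.50 | 42% | 47% |

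When these readings are treated as missing, and are missing at random, the estimate stays at about 1.0 times the true effect for every f.

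**The case against.** The rule is a fallback. The default is an ophthalmologist's reading at a clinic visit made to coincide with month 6, so only some patients are exposed. Nothing in the article says how many, and the values of f above are illustrations. This stands.

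A reader might infer that every patient without a visit between enrolment and month 6 necessarily receives the baseline value. The text does not support that. It asks for the closest reading without saying that it must come before month 6. If later readings count, visits at months 7 to 11 are all nearer than baseline. A reader might also picture readings from month 1 or 2 being used. That fits poorly with a 3-month minimum interval counted from a clinic visit, and the enumeration never produces one.

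It would also go too far to treat IOP as the protocol's check on gaming of the devices. The Discussion relies on an oath, review of medication bills, and questions about device use after all payments are made.

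With equal shares in the arms, the bias is towards no effect, on a secondary outcome for which no power is claimed. Most of the power loss comes from having no usable reading: treating the values as missing recovers only 0 to 5 points. What the correction mainly restores is an undiluted estimate.

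Finally, visit windows are often left to a fuller document, and few people would knowingly enter a baseline value as follow-up. But the article does state a selection rule, and that rule admits the baseline value. This is a rule fixed badly, which is different from a detail left out.

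**Conclusion.** The point holds in limited form. As written, the fallback can enter the baseline IOP as the month-6 IOP for patients whose next check-up falls after month 6. This follows if only readings on record by month 6 are used, or through a tie at a 12-month interval. If later readings are used, the value is taken after incentives end. The article does not say which applies.

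The size is a factor of (1 − f) on the expected arm difference for secondary objective 1, given equal f in the two arms and an average effect among those affected. Since f is not stated and may be small, no particular loss can be claimed. The adherence outcome and the sample size are untouched. It is worth correcting because the ambiguity is avoidable and would otherwise be settled case by case by unmasked staff.

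**What to change.** Amend the fallback in the month-6 checklist and the analysis plan:

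- The reading must be taken after allocation is revealed and can never be the baseline reading.
- State whether readings after month 6 are eligible and up to what limit, with a tie-break. The sponsor should choose the width, keeping informative readings taken under incentives. A window of 6 weeks either side, for example, would run from about month 4.6 to month 7.4. It would discard the month-4 reading of a patient on 4-monthly check-ups, taken three months after allocation was revealed.
- Treat anything else as missing, and extend to IOP the multiple imputation already planned for missing adherence data.
- Report by arm the share of fallback readings and their timing relative to month 6.

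The cost is small. Choosing the closest reading already requires measurement dates, so the rule can be applied to patients already enrolled, provided it is fixed before the IOP data are analysed. The downside is that some IOP values become missing, and the result then relies on the missing-at-random assumption for those patients.

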### Data management and monitoring

The study devices are received from patients at months 3 and 6. The project coordinator will scan each study device using the CertiScan™ desktop reader and the data will be downloaded to the Med-ic™ software. From the software the data will be exported to an Excel file where the project coordinator will check the validity of the data. She will notably check whether multiple medication users have kept their medication in the correct study device and will remedy the situation whenever possible. The project coordinator will then save the data as a text file and a statistician will run the file through a tailored Stata program that automates adherence calculation. For data that is collected via questionnaires and checklists, the project coordinator will oversee data entry at SNEC. Data will be keyed into separate Excel files that will be merged using the participant IDs. The data entry sheets have been designed to only accept values that are within the correct range, and data will be double-entered by two different study team members to minimize errors.

During the trial all paper-based documents and used study devices will be stored in locked cabinets at SNEC and Duke-NUS. After study completion, all paper-based documents will be stored in a secured room at Duke-NUS in a digital format (scanned documents stored on CD-ROM). All source documents will be retained until at least 6 months after the end of the study and then securely destroyed. Digital records will be kept for at least 15 years and securely destroyed upon the publication of all pertinent research studies/reports.

Once the first 25, 50, and 75 participants have successfully completed their month 6 assessment, primary and secondary outcomes will be computed in both study groups by a trained statistician. Attrition and missing data patterns will also be analysed. The purpose of these interim analyses is to detect potential issues that might have arisen during the data collection process before the end of the trial and to report preliminary results to SingHealth CIRB (Centralised Institutional Review Board) on an annual basis. No stopping rules have been defined for this trial.

The research optometrist will ask patients and caregivers about potential adverse events. If a patient has been hospitalized the research optometrist will copy and file the patient discharge summary if it is available. Reporting of adverse events involves notifying the SingHealth CIRB and submitting the serious adverse event (SAE) Reporting Form within the stipulated time frame. The notifying and reporting requirements depend on the severity, nature and causality of the event and there are specific procedures that must be followed [45].

No data monitoring committee will be utilized for this trial as the intervention has no impact on the standard of care received by SNEC glaucoma patients and therefore does not involve more than minimal risks. This trial is subject to study review visits of and/or audits by the SingHealth Research Quality Assurance unit, which is responsible for ensuring that all investigator-initiated research processes are conducted suitably, adequately, effectively, and efficiently across the SingHealth cluster. These study review visits/audits may be conducted routinely, triggered by CIRB or upon an investigator’s request.

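### The protocol lets an unmasked coordinator, who helped prepare the allocation, correct container mix-ups by judgement before the primary outcome is scored

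*Protocol article*

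**What the plan says.** **Handling of the records (Data management and monitoring).** "The study devices are received from patients at months 3 and 6". After scanning and download, "the data will be exported to an Excel file where the project coordinator will check the validity of the data". The coordinator "will notably check whether multiple medication users have kept their medication in the correct study device and will remedy the situation whenever possible". Scoring comes after that: "The project coordinator will then save the data as a text file and a statistician will run the file through a tailored Stata program".

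**Who knows the allocation (Randomization).** A random number generator "was used by the study principal investigator (PI) and coordinator at Duke-NUS to create an assignment schedule", and "the study PI and project coordinator enclosed the assignments in sequentially numbered, opaque, sealed randomization envelopes". The section adds that "the behavioural nature of the intervention precludes masking the arm allocation to both the study team and patient". Allocation is revealed at the end of the one-month baseline.

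**What the records feed.** The primary outcome is the change in percentage of adherent days from month 1 to month 6 (Primary outcome). One dose missed in its window makes the whole day non-adherent, and the percentage of adherent days also sets the VP rebate (Arm 2: value pricing). Usual care (UC) patients receive no adherence-contingent payment (Arm 1: usual care).

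**Identification of devices (Data collection).** "Each device will be labelled with a number, based on when the study device is set up". That number is unrelated to the patient ID, but the vials carry the patient's name and the medication.

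**The concern.** In an open-label trial with a behavioural outcome, the electronic time-stamp is the main protection against influence by people who know the arm. That protection is weakened if someone who may know the arm decides, case by case, which records are wrong and can be put right before they are scored. The automated program does not help, because it runs on the file as it stands after this step.

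The stakes of a correction also differ between arms. In VP it can decide whether a patient is paid; in UC it cannot. If records were corrected more readily in one arm than in the other, the difference would enter the primary comparison and could not be separated from a treatment effect.

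**Working it through.** The point is procedural and disputes no figure in the plan. The check sets the passages side by side and then asks what scale an unequal correction could have.

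**1. Order of steps.** Scan, export to Excel, validity check, remedy, save as text, Stata scoring. Judgement comes before automation.

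**2. Timing against allocation.** Devices come back at months 3 and 6, and allocation is revealed at the end of month 1. Both halves of the primary outcome (month 1 and month 6) are therefore handled after allocation is known.

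**3. What a remedy can mean.** At month 3 the devices return to the patient, so a remedy could be advice on storage. At month 6 no monitoring follows, so it can act only on the data.

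**4. Stated safeguards.** Double entry is described for questionnaire and checklist data. The sensitivity analysis under Statistical methods concerns patients who withdraw. Neither covers this step.

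**5. How a swap changes the outcome.** A made-up example: drop A is scheduled for the evening, drop B for morning and evening, and the two containers are swapped. Container B then shows no morning opening, so every swapped day fails even if all doses were taken. Re-assigning the openings restores those days. In a 30-day month each day is worth 100/30 = 3.3 points, so ten days are worth 33 points for that patient. If both drops have the same schedule, a swap changes nothing. Re-assignment cannot create an opening that was never recorded.

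**6. Effect on the arm comparison.** The model adjusts for baseline. Let δ1 and δ6 be the VP-minus-UC differences in mean correction at months 1 and 6, and β the slope of month-6 on month-1 adherence. The arm estimate then shifts by approximately δ6 − β·δ1. Correcting a persistent swap in both months partly cancels. Extra upward correction of VP records at month 1 alone would work against VP.

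**7. Scale, on assumptions only.** Take correction at month 6 alone and ignore the cancellation in step 6:

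shift = m × f × d

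- m: share of patients on several drops
- f: difference between arms in the share of those patients corrected
- d: points changed per corrected patient-month

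The documents give none of the three. Stratifying by single versus multiple drops should keep m similar in the two arms, so the shift depends on f.

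From Sample size: SD 16.3, target 10 points, 100 patients less 20% = 40 per arm. Standard error = 16.3 × √(2/40) = 3.64 points, unadjusted.

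| m | f | d | Shift (points) | Two-sided type I error |
|---|---|---|---|---|
| any | 0 | any | 0 | 5% |
| 0.2 | 0.10 | 10 | 0.2 | 5.0% |
| 0.4 | 0.25 | 10 | 1.0 | 5.9% |
| 0.4 | 0.25 | 30 | 3.0 | 13% |
| 0.6 | 0.50 | 30 | 9.0 | about 70% |

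The last row needs a 50-point gap between arms in correction rates. It is an outer bound, not a plausible case.

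**The case against.** The article never says that time-stamps are edited. The remedy refers to medication kept in the wrong device, the follow-up calls check storage, and part of what is meant may be correcting the patient's practice. This stands for month 3 but not for month 6.

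A condensed article need not print its data-handling rules. A re-assignment rule, change log or lock procedure may sit in a fuller document, so their absence here is no finding. That is fair. The point rests instead on what is stated: a discretionary correction step given to a role that had the allocation list, in a team described as unmasked.

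There are partial safeguards. A different person runs the scoring, data are downloaded to the device software before export, digital records are kept for at least 15 years, and institutional audits apply. These make later checking possible, but they do not make the correction blind to arm.

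Removing the patient ID would not be enough to mask the step. A swap cannot be recognised from a device number alone, and the coordinator scans devices whose vials carry names. This stands and shapes the fix.

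A reader might also infer that unmasked edits do enter the primary outcome and inflate the VP effect. The documents do not support that. They show an opportunity and a difference in stakes between arms, not differential editing. Baseline records pass through the same step, so the direction is open.

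**Conclusion.** The concern holds as a weakness of procedure. The protocol permits arm-aware, discretionary correction of the primary-outcome records of multiple-drop users before scoring. At month 6 that correction can act only on the data, and the same data decide VP rebates. The explicit remedy concerns only patients on several drops, and a swap matters only where their schedules differ.

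No size can be derived from the documents. The middle rows of the table (1 to 3 points) show that a moderate imbalance would matter against a 10-point target, but they rest wholly on assumed inputs and on correction at month 6 alone. Occurrence and direction are not established.

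This is a cheap improvement, not a fault that invalidates the trial. Masking really is precluded for patients and for staff who speak to them, but correcting swaps in a time-stamp file does not require knowledge of the arm.

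**What to change.** 1. The coordinator passes on the unedited export with a neutral code that links each patient's devices and their dosing schedules but carries no arm.
2. Container swaps are corrected in the existing Stata program by one pre-set rule, for example re-assigning only when each container's pattern matches the other's schedule over a fixed run of consecutive days. Every change is logged.
3. Each download is scored and locked before arm is merged and rebates are computed.
4. The raw export is kept, and the primary analysis is also reported on uncorrected data as a sensitivity analysis.

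Because the rule sits in the program, it does not matter that the coordinator knows the arms, and no extra staff are needed. The cost is some programming, a coded link file and a slight delay in computing rebates. The article reports 93 patients enrolled by 26 January 2016. For downloads already processed, steps 2 and 4 can still be applied wherever the original exports have been kept.
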